## Abstract

**Background:**

Despite increasing use of continuous glucose monitoring (CGM) and continuous subcutaneous insulin infusion (CSII, insulin pumps) in type 1 diabetes (T1D) in pregnancy, achieving recommended pregnancy glycaemic targets (3.5–7.8 mmol/L or 63–140 mg/dL) remains challenging. Consequently, the risk of adverse pregnancy outcomes remains high. Outside pregnancy, hybrid closed-loop (HCL) insulin delivery systems have led to a paradigm shift in the management of T1D, with 12% higher time in glucose target range (TIR) compared to conventional CSII. However, most commercially available HCL systems are currently not approved for use in pregnancy. This study aims to evaluate the efficacy, safety and cost-effectiveness of the MiniMed™ 780G HCL system (Medtronic) in T1D in pregnancy.

**Methods:**

In this international, open-label, randomized controlled trial (RCT), we will compare the MiniMed™ 780G HCL system to standard of care (SoC) in T1D in pregnancy. Women aged 18–45 years with T1D diagnosis of at least one year, HbA1c ≤ 86 mmol/mol (≤ 10%), and confirmed singleton pregnancy up to 11 weeks 6 days will be eligible. After providing written informed consent, all participants will wear a similar CGM system (Guardian™ 3 or Guardian™ 4 CGM) during a 10-day run-in phase. After the run-in phase, participants will be randomised 1:1 to 780G HCL (intervention) or SoC [control, continuation of current T1D treatment with multiple daily injections (MDI) or CSII and any type of CGM] stratified according to centre, baseline HbA1c (< 53 vs. ≥ 53 mmol/mol or < 7 vs. ≥ 7%), and method of insulin delivery (MDI or CSII). The primary outcome will be the time spent within the pregnancy glucose target range, as measured by the CGM at four time points in pregnancy: 14–17, 20–23, 26–29, and 33–36 weeks. Prespecified secondary outcomes will be overnight TIR, time below range (TBR: <3.5 mmol/L or < 63 mg/dL), and overnight TBR. Other outcomes will be exploratory. The planned sample size is 92 participants. The study will end after postpartum discharge from hospital. Analyses will be performed according to intention-to-treat as well as per protocol.

**Discussion:**

This large RCT will evaluate a widely used commercially available HCL system in T1D in pregnancy. Recruitment began in January 2021 and was completed in October 2022. Study completion is expected in May 2023.

**Trial registration:**

ClinicalTrials.gov: NCT04520971. Registration date: August 20, 2020. https://clinicaltrials.gov/ct2/show/NCT04520971

## Background

Pregnancies complicated by type 1 diabetes (T1D) are associated with an increased risk of adverse pregnancy outcomes such as congenital anomalies, miscarriages, preeclampsia, preterm delivery, large-for-gestational age (LGA) infants, and perinatal mortality [1–4]. To reduce the risk of these complications, women with T1D are advised to achieve near normoglycaemia before and during pregnancy, with a time in range (TIR) of 3.5–7.8 mmol/L (63–140 mg/dL) of > 70% [5]. Unfortunately, given the gestational variability in insulin sensitivity and absorption, achieving and maintaining tight glycaemic control in pregnancy is often difficult to accomplish, even with increasing use of new diabetes technologies including continuous glucose monitoring (CGM) and continuous subcutaneous insulin infusion (CSII, insulin pumps) [6–9].

Studies have shown that both multiple daily injections (MDI) and insulin pumps are effective treatment approaches for T1D in pregnancy [10–14]. However, insulin pumps offer advantages in terms of flexibility in insulin basal rates and bolusing, facilitating adaptation to the high glycaemic variability in early pregnancy and timely adjustment to the increasing insulin need later in pregnancy. Hybrid closed-loop (HCL) insulin delivery systems provide automated glucose-responsive insulin delivery overnight, between meals and additional manually triggered premeal boluses. In children, adolescents as well as adults, HCL systems have led to a paradigm shift in T1D management with better glycaemic control, less hypoglycaemia frequency and duration, and better quality of life [15–17]. HCL systems hold promise in the management of T1D in pregnancy as shown by smaller studies [18–23]. However, most commercially available HCL systems are currently not approved for use in pregnancy, and there could be concerns regarding the HCL algorithms’ ability to adapt to the rapidly changing insulin requirements typical to pregnancy. Larger, longer-duration multicentre studies are therefore needed to assess whether commercially available HCL systems can safely improve glycaemic control in T1D in pregnancy and improve pregnancy outcomes.

This study aims to evaluate the safety, efficacy, feasibility and cost-effectiveness of the MiniMed™ 780G HCL system (Medtronic) compared to standard of care (SoC) in pregnant women with T1D. We hypothesize that the 780G HCL system in T1D in pregnancy can improve glycaemic control with less hypoglycaemia, both at night and during the day. This, in turn, might improve pregnancy outcomes.

## Methods

### Study design and setting

The CRISTAL study is an open-label, multicentre randomized controlled trial (RCT) with the participation of 12 hospitals in Belgium and the Netherlands comparing the 780G HCL system with SoC in T1D in pregnancy. Pregnant women with T1D, diagnosed at least one year before study participation, and a glycated haemoglobin (HbA1c)  ≤ 86 mmol/mol (≤ 10%) will be eligible for study participation, providing their pregnancy has not progressed beyond 11 weeks and 6 days. After providing written informed consent, all participants will be asked to wear a similar (masked) CGM system [Guardian™ Link (3) transmitter with Guardian™ Sensor (3), or the Guardian™ 4 transmitter with Guardian™ 4 sensor] during a 10-day run-in phase. Masking is not required for participants already using the Guardian™ 3 or 4 CGM before the run-in phase. After the run-in phase, participants will be randomised 1:1 to the 780G HCL system (intervention) or to SoC (control, continuation of current T1D treatment approved for use in pregnancy). In both randomisation groups, the glucose target will be set to 3.5–7.8 mmol/L (63–140 mg/dL), with the aim of a TIR > 70%. Differences in glycaemia between both randomisation groups will be evaluated by similar CGM data collected during 21 days at different time points during pregnancy: at 9–12 (if inclusion < 8 weeks), 14–17, 20–23, 26–29, and 33–36 weeks. The Guardian™ 3 CGM will be masked for participants in the control group who routinely use a different glucose monitoring method. Standardised procedures (within the field of endocrinology and obstetrics) will be used for management and follow-up of all participants across all centres, independent of the randomisation group. The study will end after postpartum discharge from hospital. After delivery, the 780G HCL system can be continued in line with normal routine. An overview of the study is shown in Fig. 1. The study has been registered in ClinicalTrials.gov as NCT04520971. The study protocol was approved by the Medical Ethics Review Committees of all participating centres as well as the national competent authorities (Belgian registration number: B3222020000272; Dutch registration number NL78535.000.21).

**Fig. 1 Fig1:**
[figure not shown]
The CRISTAL study flow diagram T1D type 1 diabetes; HbA1c glycated haemoglobin; CGM continuous glucose monitoring

### Modifications to the study protocol

To facilitate recruitment, three additional centres participated: University Hospital Saint-Luc, General Hospital Turnhout Campus Sint-Jozef, and Amsterdam University Medical Centres location AMC. This has led to an amendment of the original study protocol (last approved version: fourth version, dd 14-10-2021). In addition, the Guardian™ 4 CGM was launched and received CE mark in May 2021. The Guardian™ 4 sensor has a new advanced sensor calibration algorithm but is otherwise similar to the Guardian™ 3 sensor, and is intended to minimize or eliminate required calibrations, thereby reducing the glucose management burden for the user. The Guardian™ 4 sensor is physically identical to the Guardian™ 3 sensor, and the Guardian™ 4 transmitter is equivalent to the Guardian Connect Transmitter with the addition of the G Algorithm, indicating the equivalency between the Guardian™ 3 and Guardian™ 4 CGM (data on files). Therefore, no significant biases are expected when switching from the Guardian™ 3 CGM to the Guardian™ 4 CGM in the intervention group, nor to compare data with the (masked) Guardian™ 3 CGM used during the run-in phase or when used in the control group.

### Objectives

This research answers the need to evaluate whether the 780G HCL system in pregnant women with T1D can improve glycaemic control with less hypoglycaemia compared to SoC. This, in turn, might improve pregnancy outcomes in women with T1D. All outcomes of the core outcome set (COS) for RCTs evaluating the effectiveness of interventions for the treatment of pregnant women with pregestational diabetes mellitus will be reported [24].

#### *Primary outcome*

The primary outcome will be the percentage of time spent within the T1D in pregnancy glycaemic target range (TIR) of 3.5–7.8 mmol/L (63–140 mg/dL) as measured by the (masked) CGM at four specified time points in pregnancy (14–17, 20–23, 26–29, and 33–36 weeks). TIR was chosen as primary outcome since an increase in TIR has been associated with less complications both in pregnant and non-pregnant people with T1D [9, 25].

#### *Secondary outcomes*

Three prespecified secondary outcomes as measured by the (masked) CGM at the four specified time points in pregnancy will be:

% overnight (midnight till 6 am) TIR;% time below range (TBR) (< 3.5 mmol/L or < 63 mg/dL);% overnight TBR.

#### Other secondary outcomes will be exploratory.

- Maternal glycaemic outcomes

% TIR during the day (6 am till midnight); % (overnight) TIR 9–12 weeks; mean sensor glucose level; % (overnight) time above range [TAR > 7.8 mmol/L (> 140 mg/dL)]; % time spent > 10 mmol/L (> 180 mg/dL), < 3.9 mmol/L (< 70 mg/dL), < 3.3 mmol/L (< 60 mg/dL), < 3.0 mmol/L (< 54 mg/dL), and < 2.8 mmol/L (< 50 mg/dL); % time in non-pregnant target range 3.9–10 mmol/L (70–180 mg/dL); low blood glucose Index (LBGI) [26]; CGM compliance; HbA1c ; total daily insulin dose (TDD). To evaluate glycaemic variability, standard deviation (SD), coefficient of variation (CV), and mean amplitude of glucose excursions (MAGE) will be measured [27]. Maternal glycaemic outcomes will be evaluated in each trimester and at the different time points during pregnancy, and will be compared with baseline and between both randomisation groups.

- Safety outcomes

Number and duration of hypoglycaemic episodes [time spent  < 3.5 mmol/L (< 63 mg/dL) and < 2.8 mmol/L (< 50 mg/dL)], nocturnal and/or severe hypoglycaemic episodes, and other adverse events such as diabetic ketoacidosis (DKA).

- Patient-reported outcomes

The following questionnaires will be completed at the different study visits:

A self-designed questionnaire on general habits and socio-economic background previously used in the Belgian Diabetes in Pregnancy Study (BEDIP-N) study to extensively collect information on socio-economic status and habits [28];The Hypoglycaemia Fear Survey II (HFS-II) consisting of a 10‐item ‘behaviour’ subscale that measures behaviour involved in avoidance and overtreatment of hypoglycaemia and a 13‐item ‘worry’ subscale that measures anxiety and fear surrounding hypoglycaemia with higher scores indicating higher fear of hypoglycaemia [29];The 36-Item Short Form Health Survey (SF-36) includes a set of generic, coherent, and easily administered quality of life measures that is validated for use in the maternity context [30];The 20-item Centre for Epidemiologic Studies-Depression (CES-D) questionnaire which is validated in pregnancy to asses symptoms of clinical depression over the past seven days and consists of 20 items with each item being scored between 0 (rarely or not applicable) and 3 (almost all the time applicable) on a four-point Likert scale, resulting in a total score within the range 0–60, with a score of ≥ 16 being suggestive for clinical depression [31];The Problem Areas in Diabetes-short form (PAID-5) contains items assessing fear, depressed mood and the demands of living with diabetes [32];The Food Frequency questionnaire (FFQ) validated for the Belgian population includes questions on frequency and portion size of consumed foods and beverages [33];The diabetes treatment satisfaction questionnaire (DTSQ) status which measures satisfaction with diabetes treatment regimens in people with diabetes [34].The DTSQ change which has been developed to overcome potential ceiling effects (where respondents score maximum or near-maximum satisfaction at baseline and can show little or no improvement at follow-up) [35].

In addition, hypoglycaemia awareness status at each study visit will be determined by the Gold questionnaire, in which an individual’s experience in detecting hypoglycaemic events is scored from 1 (always aware) to 7 (never aware) in a Likert-type scale [36].

- Pregnancy outcomes

Obstetric outcomes: gestational weight gain; maternal hypertensive disorders including worsening of pre-existing hypertension, gestational hypertension, preeclampsia [≥ 20 weeks of gestation: new onset of hypertension and proteinuria or the new onset of hypertension and significant end-organ dysfunction with or without proteinuria (dipstick ≥ 2+, ≥ 0.3 g protein/24 hours or ≥ 30 mg/dL protein in spot urine or spot urine protein/creatinine ratio ≥ 30 mg protein/mmol creatinine)], and eclampsia (one or more generalized convulsions and/or coma in the setting of preeclampsia and in the absence of other neurologic conditions); other pregnancy complications [including Haemolysis, Elevated Liver enzymes and Low Platelets (HELLP) syndrome, polyhydramnios, and oligohydramnios]; hospital admissions and length of hospital stay (postpartum included); intra-uterine growth restriction (IUGR); fetal malformation; pregnancy duration; preterm delivery (< 37 weeks); type of labour [spontaneous, induced or planned caesarean section (C-section)]; mode of delivery (vaginal, instrumental, planned C-section or emergency C-section) and indications; miscarriage (< 20 weeks), stillbirth (fetal demise ≥ 20 weeks), and neonatal death (< 1 month after delivery); umbilical cord blood analysis including measurement of C-peptide.

Neonatal outcomes: sex; birth weight and percentile; macrosomia (> 4 kg); incidence of LGA, gestational age adjusted birth weight > 97th percentile, and small for gestational age (SGA), both also adjusted for infant’s sex and parity [37]; 10 min Apgar score; shoulder dystocia; birth trauma; congenital malformations; neonatal respiratory distress syndrome [at least four hours of respiratory support with supplemental oxygen, continuous positive airway pressure (CPAP), or intermittent positive-pressure ventilation during the first 24 h after delivery]; neonatal hypoglycaemia (glycaemia < 2.2 mmol/L or < 40 mg/dL or need for intravenous dextrose); neonatal jaundice (hyperbilirubinemia, need for phototherapy); duration and indication for admission on the NICU (admission defined as > 24 h); sum of skinfolds; neonatal fat mass; breastfeeding. These outcomes are included both as individual and as a composite outcome consisting of pregnancy loss (miscarriage, stillbirth or neonatal death), LGA, shoulder dystocia, birth trauma, respiratory distress, neonatal hypoglycaemia, and NICU admission.

- Health economic outcomes

The health economic evaluation of the HCL system (intervention) compared to SoC will be performed applying a cost-utility analysis consisting of two phases: (1) a trial-based economic evaluation, a cost-utility analysis of the intervention versus control alongside the RCT (including data on pregnancy outcomes), and (2) a model-based cost-utility analysis to predict costs and health effects of the intervention versus control on the longer term (including longer term health of the offspring). In both phases, health effects will be expressed as quality-adjusted life years (QALY) as recommended by the ISPOR-guidelines ‘Good research practices for cost-effectiveness alongside clinical trials’ [38]. Data on health-related quality of life will be collected using the SF-36 questionnaire [30]. Medical consumption and related costs will be collected as well as costs linked to the intervention. The analysis will be performed from a societal perspective, meaning that direct and indirect medical costs will be included.

### Recruitment and eligibility

Participants will be recruited from 11 endocrinology departments in Belgium (four university centres: University Hospitals Leuven, University Hospital Brussels, Ghent University Hospital, and University Hospital Saint-Luc; and seven large non-university hospitals: Imelda Hospital Bonheiden, OLV Hospital Aalst, Vitaz Campus Sint-Niklaas Moerland, General Hospital Groeninge Kortrijk, General Hospital Sint-Jan Brugge, General Hospital Delta Campus Rumbeke, and General Hospital Turnhout Campus Sint-Jozef) and one university centre in the Netherlands (Amsterdam University Medical Centres location AMC). The planned recruitment period is maximum two years. Written informed consent will be obtained at each site before any study-related activities are performed. Participants will be eligible if they fulfil the following criteria:

#### *Inclusion criteria*

Women with T1D diagnosis of at least one year.Age 18–45 years.Singleton pregnancy up to 11 weeks and 6 days confirmed by β-hCG in blood and/or ultrasound.Intensive insulin treatment approved for use in pregnancy (MDI or CSII).Baseline HbA1c ≤ 86 mmol/mol (≤ 10%).Dutch, French or English speaking and understanding and e-mail access.

#### *Exclusion criteria*

Use of a HCL system as closed-loop (allowed to use this system in open-loop).Multiple pregnancy.A physical or psychological disease likely to interfere with the conduct of the study according to evaluation by the treating physician.Medications known to interfere with glucose metabolism (intermittent use of prophylactic steroids for fetal lung maturation allowed).Insulin TDD ≥ 1.5 units/kg.Known allergy to adhesives for infusion set and/or CGM.

### Randomisation

Randomisation will be performed centrally by software and a randomisation algorithm developed by I Biostat. Participants will be randomised 1:1 to either the 780G (intervention) or SoC (control) group. Deterministic minimisation of variation will be used based on the following baseline characteristics: study centre, baseline HbA1c (locally determined at screening) stratified according to HbA1c < 53 vs. ≥ 53 mmol/mol (< 7 or ≥ 7%), and method of insulin delivery (MDI or insulin pump) [39].

### Groups

#### *Intervention*

Participants allocated to the intervention will be switched from their current diabetes therapy to the MiniMed™ 780G (Medtronic) HCL system. It received approval by the European Medicines Agency (EMA) in May 2020 and is currently under review for Food and Drug Administration (FDA) approval. This HCL system includes Proportional-Integral-Derivative (PID) technology with insulin feedback (the most advanced SmartGuard™ technology) consisting of the 780G insulin pump and Accu-Chek Guide Link meter with Guardian™ Link (3) transmitter and Guardian™ Sensor (3) or newer Guardian™ 4 transmitter and Guardian™ 4 sensor. The system allows for a glycaemic target at 5.5, 6.1 or 6.7 mmol/L (100, 110 or 120 mg/dL, respectively). To achieve tight glycaemic control in pregnancy, the following settings will be recommended in the study: glycaemic target set at 5.5 mmol/L (100 mg/dL) and active insulin time (AIT) set at 2 h. These settings may be adjusted during the study according to individual needs. In addition, the following recommendations will be made to limit the risk of postprandial hyperglycaemia: (1) optimise the insulin to carbohydrate ratios (ICR) by lowering the ratios as much as possible; (2) if further reduction of the ICR is impossible (due to occurrence of safe meal bolus, i.e. a bolus administered by the system which is lower than calculated based on the ICR due to prediction of an elevated risk of hypoglycemia), further reduction of carbohydrate intake with meals will be advised; (3) add fake carbs for a correction bolus in between meals or with meals. The amount and frequency of adding fake carbs will be registered at each visit at the diabetes clinic.

#### *Control*

Usual SoC was selected as control since RCTs have shown that both MDI and insulin pump therapy are equally effective to manage T1D in pregnancy [14]. Participants randomised to the control group will continue their current therapy [MDI or CSII with self-monitoring of blood glucose (SMBG) or any type of CGM; sensor-augmented pump therapy (predictive stop before low or on low) or a HCL system used in open-loop].

### Safety

Safety parameters will be assessed and reported at all study visits in line with the Medical Device Regulation (EU) 2017/745 and the MDCG 2020-10/1 European guideline. All (serious) adverse events [(S)AEs] and device deficiencies (DDs) will be recorded on applicable standardized reporting forms and associated with the subject identification number, with additional detailed description of the event. SAEs and reportable DDs will be reported onwards to the sponsor, manufacturer, central Medical Ethics Review Committee and national competent authorities as required.

### Discontinuation of participation

In case of premature discontinuation [due to withdrawal of participant’s consent, a significant medical reason or start of medication that does not allow for normal glucose metabolism evaluation (intermittent use of prophylactic steroids for fetal lung maturation allowed), a change in participant’s condition which justifies discontinuation of treatment, and noncompliance (e.g. not attending out-patient clinics)], data on glycaemic control and pregnancy outcomes will be further collected if an additional informed consent is provided.

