### Statistics

#### *Sample size*

The sample size is determined to have about 90% power for the primary and three key secondary outcomes. To this purpose, at least 92 patients in total will be randomised. The sample size calculation was performed for these four outcomes separately, considering a Bonferroni correction for multiple testing to guarantee a 5% two-tailed family-wise significance level, and withholding the largest sample size. Calculations were performed for showing a time-averaged difference between the two groups over four longitudinal measurements [44]. A correlation of 0.6 was assumed between repeated measurements and a 20% loss to follow-up during the study was anticipated. For the primary outcome, the sample size was determined to detect an absolute between-group difference in mean TIR of 10% during pregnancy, assuming a SD of 13% for the TIR [22]. The power to show a difference of 1.1% between both groups for TBR, assuming a SD of 1.6% equals 91%. The power to show a difference of 1.6% between both groups for overnight TBR, assuming a SD of 2.5%, equals 87%. The power to show a difference of 15.2% between both groups in overnight TIR, assuming a SD of 18.4%, equals 97% [20]. After randomisation of approximately 50% of participants, a blinded sample size recalculation will be performed to re-estimate variances and correlations [45]. The sample size will be adjusted if needed to achieve the anticipated power.

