#### *Data analysis*

Analyses will be performed according to intention-to-treat as well as per protocol. Clinical and demographic data at baseline will be summarised in a table using frequencies with percentages, mean values with SD or medians with the interquartile range (IQR). A linear mixed model for repeated measurements will be used for the primary outcome analysis, with TIR as response variable, and group, time point of measurement, stratification factors baseline HbA1c and method of insulin delivery, and finally baseline TIR as main effects, and a random effect of centre. A 1.25% significance level will be adopted. The mean difference between the groups will be presented with a 95% confidence interval. Using likelihood methods for estimation, this analysis provided valid results under a missing-at-random (MAR) drop-out pattern [46]. An analogous analysis method will be applied to the prespecified secondary outcome variables, with adjustment for the baseline value of the variable associated with the outcome, rather than baseline TIR. A similar analysis method will be applied to all longitudinally measured and continuous exploratory outcomes. Analysis of cross-sectional continuous outcomes will be performed by a two-sample two-sided t-test or a Mann-Whitney U test in case of skewed distributions. For comparing binary pregnancy outcomes between both groups, a Fisher exact test will be used, whereas a two-sample t-test or Mann-Whitney U test will be used for normally distributed or not-normally distributed continuous pregnancy outcomes, respectively. As a prespecified subgroup analysis, we plan to compare the primary and three key secondary outcomes between women who started the intervention early (screening < 8 weeks) versus later in pregnancy (screening ≥ 8 weeks).

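### Outcome collection after any premature discontinuation, including for noncompliance or medical reasons, depends on a second consent, so data for the announced intention-to-treat analysis may be selectively missing

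*Protocol article*

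**What the plan says.** The section Discontinuation of participation puts several events under one rule. The list opens with discontinuation "due to withdrawal of participant’s consent", goes on to a significant medical reason or the start of interfering medication, and ends with "a change in participant’s condition which justifies discontinuation of treatment, and noncompliance (e.g. not attending out-patient clinics". For all of them, "data on glycaemic control and pregnancy outcomes will be further collected if an additional informed consent is provided". No other section keeps women in the last three categories in follow-up under the consent they have already signed.

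The Data analysis section states: "Analyses will be performed according to intention-to-treat as well as per protocol". For the primary outcome it uses a likelihood-based linear mixed model and says that "this analysis provided valid results under a missing-at-random (MAR) drop-out pattern". For delivery and neonatal endpoints: "For comparing binary pregnancy outcomes between both groups, a Fisher exact test will be used". The Sample size section states that "at least 92 patients in total will be randomised" and "A correlation of 0.6 was assumed between repeated measurements and a 20% loss to follow-up during the study was anticipated".

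**The concern.** Intention-to-treat compares women as randomised, whatever happens to treatment afterwards, and so needs outcomes from those who stop or do not comply. Here those outcomes depend on a fresh signature. It is requested after randomisation, in an open-label trial, and partly from women identified by their absence from clinic. For a woman who withdraws consent there is no alternative. For the other reasons the requirement is a design choice.

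Two kinds of outcome are exposed differently:

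- **TIR and the key secondary CGM outcomes.** Windows before discontinuation stay in the model. Later ones are missing because treatment or participation stopped. The model has no term for that event, so it extrapolates from women in the same arm who continued. Without the later data, the missing-at-random assumption cannot be checked at the point where it matters.
- **Pregnancy outcomes.** There is one value per woman, and a Fisher exact test cannot draw on earlier measurements. A woman who discontinues before delivery and does not sign again contributes nothing to pregnancy loss, large-for-gestational-age birth, neonatal intensive care admission or the composite. The Objectives section commits to reporting the full core outcome set.

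**Working it through.** **Inputs from the article (Sample size, Data analysis, Randomisation).** 92 women allocated 1:1 (46 per arm); four windows; correlation 0.6; TIR difference 10 points with SD 13; two-sided level 1.25%; 20% loss to follow-up.

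**The plan's own figures.** For a time-averaged difference over four windows the variance factor is (1 + 3 × 0.6)/4 = 0.70.

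- TIR at 90% power: 2 × (2.498 + 1.282)² × 169 × 0.70 / 10² = 33.8, so 34 per arm, 68 in total, and 68/0.8 = 85 after 20% loss. The planned 92 exceeds this, which fits keeping the largest of four sample sizes.
- Power at 92 with loss staggered over the windows (0, 6.7, 13.3, 20%) is 91.6% for time below range (TBR), 86.7% for overnight TBR and 98.5% for overnight TIR. The stated values are 91%, 87% and 97%.

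The sample size therefore reproduces. The issue is bias, which a larger sample does not cure.

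**Assumptions not in the article.** The on-treatment TIR effect is 10 points. In each arm 20% discontinue, borrowing the loss figure; that is 0.20 × 92 = 18.4 women, or 9.2 per arm. Women who stop the intervention keep a residual benefit r of 0 or 5 points. Discontinuation is either staggered (5% before each window) or all before the first window. Neither stopping nor refusal otherwise depends on TIR.

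**Formulas.**

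- Everyone followed, all stop before the first window: 0.8 × 10 + 0.2 × r = 8.00 or 9.00.
- Everyone followed, staggered: the share off treatment is 5, 10, 15 and 20%, mean 12.5%. The effect is 10 − 0.125 × (10 − r) = 8.75 or 9.375.
- All refuse: every window left in the intervention arm is on treatment, so the estimate is 10.
- Half refuse, all stop early: 10% of women have no data, giving (0.8 × 10 + 0.1 × r)/0.9 = 8.89 or 9.44.
- Half refuse, staggered: expected generalised least-squares estimate with constant correlation 0.6, time effects and a group effect, which gives 9.35 or 9.68.

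| Timing | r | Everyone followed | Half refuse (excess) | All refuse (excess) |
|---|---|---|---|---|
| Staggered | 0 | 8.75 | 9.35 (0.60) | 10 (1.25) |
| Staggered | 5 | 9.375 | 9.68 (0.30) | 10 (0.625) |
| Before first window | 0 | 8.00 | 8.89 (0.89) | 10 (2.00) |
| Before first window | 5 | 9.00 | 9.44 (0.44) | 10 (1.00) |

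**Check by simulation** (1,500 trials of 46 per arm in each scenario). In the order of the rows, the means were 8.66, 9.36, 7.94 and 9.04 with everyone followed; 9.42, 9.63, 9.06 and 9.52 with half refusing; and 10.09, 10.11, 9.91 and 9.95 with all refusing. Each mean has a simulation error of about 13 × √0.70 × √(2/46)/√1500 = 0.06. The half-refusal excesses were 0.76, 0.27, 1.12 and 0.48. Allowing for that noise, the simulated range is roughly 0.2 to 1.2, and the expected values of 0.30 to 0.89 lie inside it.

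**Pregnancy outcomes.** If the 18.4 women discontinue before delivery, the number without a pregnancy outcome is 18.4 × refusal share: 0, 9.2 or 18.4. The direction of any bias cannot be computed, because the article gives no event rates by discontinuation status.

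**The case against.** The strongest reply is that the rule offers a way to keep collecting data. A woman who agrees is followed, and no refusal rate is stated. That stands: the text supports possible loss, not certain loss. That non-attenders are least likely to sign, or that these women differ most, is plausible but written nowhere.

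A reader might also infer a fixed overstatement of 2 points (10 against 8, or 25%). That corner needs all discontinuation to come before the first window, no residual benefit, universal refusal, and the whole 20% loss to follow-up to consist of discontinuation. The planned model also keeps earlier windows and adjusts for baseline TIR, so it is not an analysis of completers only.

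A reader might further infer that a woman who stops the device but keeps attending is removed from the study. The listed reasons do not say so; only the change-in-condition reason mentions stopping treatment. Nor is it established that delivery records are out of reach, since the consent form and full protocol are not shown.

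The article states the missing-at-random assumption openly, and sensitivity analyses commonly belong to the statistical analysis plan, so their absence here is no fault. Finally, recruitment closed in October 2022 and completion was expected in May 2023, which limits what an amendment can achieve.

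These points reduce the certainty and the size. They do not remove the printed rule, which applies one second-consent condition to reasons that do not require it and so works against the announced intention-to-treat analysis.

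**Conclusion.** The concern holds as a risk of selective missingness created by a stated rule. It is clearest for pregnancy outcomes, where a woman who does not sign again is absent altogether. For TIR, under the assumed 10-point effect and 20% discontinuation per arm, the overstatement runs from 0 (nobody refuses), through about 0.3 to 0.9 points (half refuse), to about 0.6 to 2 points (all refuse). Within each range it depends on timing and residual benefit. Where in this span the trial falls cannot be determined, because the refusal rate, the discontinuation rate and the post-discontinuation TIR are not given. The point is worth correcting because the change is specific and concerns data collection only.

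**What to change.** In Discontinuation of participation, separate stopping treatment and noncompliance from withdrawal of consent. State that after the former, outcome collection continues under the main consent (CGM windows where feasible, and delivery and neonatal records) unless the woman withdraws consent to data collection. For women still in follow-up, seek that agreement now, before any discontinuation. This is itself a further consent, but it is asked of everyone and does not depend on having stopped.

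As an optional addition, run a reference-based sensitivity analysis that imputes values from the control arm for women with no post-discontinuation data. It remains possible if the amendment comes too late for some.

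The cost is consent wording, an ethics amendment across the 12 hospitals in two countries and, if wanted, one further analysis. It will not recover data from women already lost, and it cannot make a non-attending woman complete a 21-day CGM window. Its surest gain is in pregnancy outcomes that can be read from records.
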